### 2.12. Follow-up Period

All patients recruited for the research clinical trial (RCT) will be reassessed during external consultations at month 3 ± 1 week (1^st^ visit) and at month 6 ± 1 week (final visit).

All the participants will get the same reassessment at the event day (evaluation a), recruitment visit (evaluation b), 3 months later (evaluation c), and 6 months of follow-up (evaluation d) taking into consideration that not all the tools are administered at each time.

### 2.13. Sample Size

To obtain a power of 80% to detect statistically significant differences when comparing the null hypothesis—a bilateral chi-squared test for two independent samples—taking into account that the level of significance is 5% and assuming that the proportion of dependence in the control group is 41.5% [23] and the proportion in the intervention group is 15%, a total of 72 stroke survivors will be needed. Taking into account the expected percentage of dropouts of 10%, it will be necessary to recruit 80 patients. The dependence will be measured by SSSMQ and Family needs of stroke patient questionnaire.

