### 2.6. Recruitment

All the patients who have suffered a first ischemic stroke with a neurologic deficit and have been admitted in the Acute Stroke Unit of the Neurology Department of our Cruces University Hospital will be assessed by a Rehabilitation Medical Doctor (RMD) with expertise in neuro-rehabilitation. The assessment will be done in the first 48–72 h from the stroke. The survivors who need conventional rehabilitation treatment will start it within the first 72 h from the cerebrovascular attack unless they present a medical contraindication, such as hemodynamic instability or others.

The rehabilitation treatment will be at a maximum tolerated intensity, daily from Monday to Friday till the end of the hospitalization. Before the discharge of the patient, an RMD will reassess the discharge destination to home, rehabilitation hospital as inpatient, or nurse home care.

At 6 months after the stroke, all the survivors who fulfill the inclusion criteria and who are willing to take part in the research will be recruited, including their caregivers. Those who will not be included are patients without familial support, or a caregiver and the formal caregivers of stroke patients will not be included if the patient does not want to take part in the study. The sample will be divided into intervention and control groups in consecutive order (Figure 1).

Participants will be enrolled in the external consultation at neuro-rehabilitation at Cruces University Hospital in Spain. We will include eligible individuals admitted in consecutive order, to avoid bias, taking into account the inclusion and exclusion criteria. All the participants will be volunteers, having signed the informed consent. The researchers responsible for the recruitment of patients will assure that the informed consent is collected with all the rigor it requires.

The assignment to the control/intervention group will be made through a probabilistic computer algorithm with a ratio of 1: 1 between groups. The Bioinformatics and Statistics Platform of Biocruces Bizkaia Institute will be responsible for the creation of the algorithm using a simple allocation mechanism in permuted blocks of variable size. Opaque envelopes will be used to guarantee the concealment of the generated sequence. The randomization list will remain on the platform at all times, guaranteeing the concealment of the sequence of randomization.

Afterward, the devices will be installed at participants’ homes.

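### The 72 evaluable patients give about 71% power, not 80%, for the stated two-sided chi-squared test of 41.5% against 15%

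*Protocol article*

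**What the plan says.** Section 2.13 (Sample Size) gives every input of a two-proportion calculation, and its result:

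- the aim: "To obtain a power of 80% to detect statistically significant differences";
- the test: "a bilateral chi-squared test for two independent samples", at a 5% significance level;
- the assumed proportions of dependence: 41.5% in the control group and 15% in the intervention group;
- the result: "the proportion in the intervention group is 15%, a total of 72 stroke survivors will be needed";
- a 10% dropout allowance, which raises the recruitment target to 80.

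Section 2.6 (Recruitment) supplies the allocation: "with a ratio of 1: 1 between groups". So 72 evaluable patients means 36 per arm.

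**The concern.** The inputs and the result are stated together, so nothing has been left to a fuller document, and they do not agree. A difference of 26.5 percentage points, tested two-sided at 5% with 80% power, needs more than 36 patients per arm.

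This calculation is the only justification given for the size of the trial. Readers are told that, if the assumed effect is real, the chance of missing it is 20%. On the same assumptions it is nearly half as large again. The Discussion makes a later trial with 3 to 5 years of follow-up depend on positive six-month results, so a false negative here has consequences for the programme.

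**Working it through.** **Inputs.** p₁ = 0.415, p₂ = 0.15, two-sided α = 0.05, power 0.80 (section 2.13); 1:1 allocation (section 2.6). No input has to be assumed.

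Derived quantities:
- difference d = 0.415 − 0.15 = 0.265, so d² = 0.070225;
- mean proportion p̄ = (0.415 + 0.15)/2 = 0.2825, so 2p̄(1 − p̄) = 0.40539, square root 0.63670;
- v = 0.415 × 0.585 + 0.15 × 0.85 = 0.370275, square root 0.60850;
- normal quantiles: 1.9600 (two-sided 5%), 1.6449 (one-sided 5%), 0.8416 (80% power).

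**Step 1: trying to reproduce 72 with the stated two-sided test.** The pooled-variance formula is

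n per arm = [z_α √(2p̄(1 − p̄)) + z_β √v]² / d²

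= (1.9600 × 0.63670 + 0.8416 × 0.60850)² / 0.070225 = (1.2479 + 0.5121)² / 0.070225 = 44.1, hence 45 per arm.

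Other standard two-sided formulas:

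| Formula | n per arm | Rounded up | Total |
|---|---|---|---|
| Pooled variance under the null, unpooled under the alternative | 44.1 | 45 | 90 |
| Unpooled: v(z_α + z_β)²/d² | 41.4 | 42 | 84 |
| Arcsine: 2(z_α + z_β)²/h², h = 2 arcsin√p₁ − 2 arcsin√p₂ | 42.9 | 43 | 86 |
| Pooled variance in both terms: 2p̄(1 − p̄)(z_α + z_β)²/d² | 45.3 | 46 | 92 |
| Pooled with continuity correction | 51.4 | 52 | 104 |

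The smallest total is 84, which is 12 more than stated. Unequal allocation does not help: ratios of 0.5, 2 and 3 give totals of 96 to 112.

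**Step 2: what does give 72.** Replacing 1.9600 by 1.6449 (one-sided 5%) gives 34.6, so 35 per arm and 70 in total, with the pooled formula. With pooled variance in both terms it gives 35.7, so 36 per arm and exactly 72. One-sided power at 36 per arm is 81.4%. This is a plausible origin, but the article does not name its formula, so it remains an inference.

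**Step 3: power at the stated size.**

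power = Φ{[d√n − z_α √(2p̄(1 − p̄))] / √v}

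At n = 36: (0.265 × 6 − 1.2479)/0.60850 = 0.3421/0.60850 = 0.562, and Φ(0.562) = 0.713.

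| Two-sided 5% test, 41.5% v 15% | Power at 36 per arm |
|---|---|
| Pooled normal approximation | 71.3% |
| Exact enumeration, uncorrected chi-squared | 72.6% |
| Arcsine approximation | 72.7% |
| Unpooled approximation | 74.3% |
| Exact enumeration, Fisher's test | 63.3% |

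None reaches 80%. By the pooled approximation the type II error is 100 − 71.3 = 28.7%.

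**Step 4: the dropout step.** 72/0.9 = 80, so this step is correct, but it starts from the wrong base. From 90 it would give 90/0.9 = 100. If all 80 recruited patients were evaluable (40 per arm), power would be 75.9%.

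**Step 5: the effect for which 72 is enough.** Holding p₁ at 0.415 and n at 36 per arm, the pooled formula gives 80.1% power at p₂ = 0.126. So 72 evaluable patients support 80% power for 41.5% versus about 12.6%, not versus 15%.

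**The case against.** - **The error may lie in the word for two-sided, not in the 80%.** A one-sided calculation matches 72, the hypothesis in section 2.1 is worded directionally, and the 5% threshold in section 2.14 has no stated sidedness. But section 2.13 states a two-sided test explicitly and no one-sided test appears anywhere. As written, the power statement is false. The sponsor can usefully trace the origin.
- **The Fisher figure of 63% is not the main case.** Section 2.14 allows Fisher's test as an alternative, but that test is commonly kept for small expected counts, and here the smallest is about 36 × 0.2825 = 10. This is fair. The relevant range for the test named in section 2.13 is 71% to 73%, and 63% is only a lower bound if Fisher's test were used. The continuity-corrected total of 104 is likewise only a variant.
- **Section 2.4 says data from 40 patients will be analysed.** That contradicts section 2.13 and would mean about 46% power at 20 per arm. It is a separate inconsistency, and it lowers power rather than rescuing the 72.
- **The calculation concerns a binary outcome, while the primary measures are questionnaires.** If these are analysed as scores, this calculation does not give the power of that analysis. That limits the conclusion to the calculation's own assumptions, but those are what the article offers as its justification.
- **It is called a pilot.** The title also says Phase III, and the article makes a formal power claim. Either label leaves that claim in need of correction.

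**Conclusion.** The concern holds. The 72 in section 2.13 does not follow from the inputs beside it under any standard two-sided formula; they require 84 to 92 evaluable patients, or 104 with continuity correction. With 72, power is about 71% (73% by exact calculation of the uncorrected chi-squared test), a shortfall of roughly 7 to 9 percentage points. This rests only on the stated proportions, the two-sided 5% chi-squared test, 1:1 allocation and 36 evaluable patients per arm. It does not depend on the one-sided explanation. Because the error is in the stated basis for the trial's size, it must be corrected.

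**What to change.** Keep the planned number and replace the power claim in section 2.13 with a true one, for example: *72 evaluable patients (36 per arm) give about 71% power, two-sided 5% chi-squared test, for 41.5% versus 15%, or 80% power for 41.5% versus 12.6%.* Name the formula used (the figures here are from the pooled-variance normal approximation). The recruitment target of 80 can stand as the 10% dropout allowance on 72.

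Before printing the sentence, reconcile the 40 patients of section 2.4 with the 72 and 80 of section 2.13, so that the power quoted belongs to the number actually planned.

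The cost is one corrected sentence and a less favourable stated power. No extra enrolment is needed. If the sponsor prefers to keep the 80% claim for 41.5% versus 15%, the pooled formula requires 90 evaluable patients and 100 recruited.

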### 2.10. Outcome Measures

The primary clinical focus in this pilot trial is the evaluation of self-management of the stroke survivors. The proposed primary outcome will be measured by the validated Southampton Stroke Self-Management Questionnaire (SSSMQ) and Family needs of stroke patient questionnaire.

A series of secondary outcomes will be evaluated at different time points, such as the effectiveness of stroke self-management interventions. They rely upon the following items:-Physical function (PF) assessed by the modified BI and Lawton index.-Risk factor reduction (blood pressure, analytical profile -glycemia, HbA1c, lipids, weight, heart rate control, medication compliance).-Self-management behaviors by self-reported information on lifestyles: diet assessed by the Mediterranean diet assessment tool, exercise assessed by tracking with the wearables, smoking, and alcohol consumption.-Healthcare resource utilization by the information available in the public health system in Osakidetza, Cruces university hospital.-Knowledge of condition to assess whether there is a relationship between health literacy and control of cardiovascular risk factors, number of complications, number of recurrences, low adherence to pharmacological and non-pharmacological treatment, and self-management behaviors.-Mood and social isolation by Goldberg scale that measures anxiety and depression.-Stroke Self-management questionnaire (SSMQ).

Other secondary outcomes will be focused on the International Consortium for Health Outcomes Measurement (ICHOM), such as survival, disease control, and acute complications.

All the questionnaires and measurements for the achievement of the outcomes will be collected through face-to-face medical visits in the neuro-rehabilitation department.

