### 2.14. Statistical Analysis

Each variable will be characterized using frequency distributions central tendency, such as the mean and median, and to determine variability standard deviation or the interquartile range according to its distributional characteristics.

Comparisons between groups and intra-groups will be performed using parametric tests provided that the distributional characteristics of the data meet the requirements; otherwise, non-parametric tests will be used.

Comparisons between two continuous variables will be performed using the Pearson or Spearman correlation, depending on the distributional characteristics.

The comparison of proportions between categorical variables will be carried out by means of a chi-squared test or its corresponding Fisher correction. The continuous variables will be compared using the comparison of the means (t-student test or ANOVA) if the sample distribution is normal, and if the distribution is not normal, then the non-parametric Mann-Whitney U test will be utilized.

The populations will be analyzed by intention to treat analysis and as stated in the protocol.

A micro-data collection form will be developed. The analysis of costs will be done from the perspective of the health system and direct costs. The data collected will serve to estimate the actual cost of procedure data under usual practice conditions and costs derived from the implementation of the new intervention in the different contexts under study.

The collection of these data, together with data on effectiveness and utility, will enable subsequent studies on economic analysis and cost-effectiveness/utility to help decision-making on which alternatives are most effective and efficient from the point of view of the health system.

The SPSS 23.0 program for Windows (SPSS Inc, Chicago, IL, USA) will be used. A p-value of 5% or lower is considered to be statistically significant. The statistical analysis will be blind to the intervention group.

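### The 80% power is calculated for a proportion of dependent patients that the article never links to its primary outcome, two self-management questionnaires

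*Protocol article*

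**What the plan says.** **Sample size (section 2.13).** The calculation begins "To obtain a power of 80% to detect statistically significant differences" and uses "a bilateral chi-squared test for two independent samples" at a 5% level. The assumed proportions of dependence are 41.5% (control, from a cited source) and 15% (intervention). The result is 72 stroke survivors, or 80 after 10% dropout. The section ends: "The dependence will be measured by SSSMQ and Family needs of stroke patient questionnaire".

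**Primary outcome (section 2.10).** "The proposed primary outcome will be measured by the validated Southampton Stroke Self-Management Questionnaire (SSSMQ) and Family needs of stroke patient questionnaire". The section opens by naming self-management of the survivors as the clinical focus. Daily function is a secondary outcome: "Physical function (PF) assessed by the modified BI and Lawton index".

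**Who answers, and when (Tables 1 and 2).** The SSSMQ is in the survivors' schedule and the Family needs questionnaire in the caregivers' schedule, each under Self-Management. Both are given at baseline, at the first visit (3 months later) and at the final visit (6 months later). Table 1 lists the modified Barthel and Lawton indices separately, under Activities of Daily Living.

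**Analysis (section 2.14).** Categorical variables are compared by chi-squared or Fisher test, continuous ones by t-test or ANOVA, or by Mann-Whitney if not normal. The threshold is general: "A p-value of 5% or lower is considered to be statistically significant".

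**The concern.** A sample size calculation is informative only if its endpoint is the one that will be tested. Here the calculation needs a yes/no state, dependence, with a known rate in control survivors. The primary outcome is a pair of questionnaires on a different construct, from two different respondents. The closing sentence of section 2.13 is the only bridge between them. It names the instruments but does not say what score makes a patient dependent, or how a survivor's answers and a caregiver's answers yield one classification.

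The trial then has no usable power statement for its primary question. A null result could not be read as evidence against an effect of the size the planners had in mind, because no such size is stated on either questionnaire. With two primary measures, it is also unclear what the 5% and the 80% refer to.

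**Working it through.** **1. The plan's own figure.** Inputs from section 2.13: p1 = 0.415, p2 = 0.15, two-sided 5% (z = 1.960), 80% power (z = 0.842). Allocation is 1:1 (section 2.6). The mean proportion is 0.2825 and the difference 0.265.

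n per arm = [1.960 × √(2 × 0.2825 × 0.7175) + 0.842 × √(0.415 × 0.585 + 0.15 × 0.85)]² / 0.265²
= [1.960 × √0.4054 + 0.842 × √0.3703]² / 0.0702 = 3.098 / 0.0702 = 44.1, so 45 per arm and 90 in total.

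The stated 72 is not reproduced. Other two-sided versions give 84 (unpooled variance), 86 (arcsine) and 104 (continuity correction). Only a one-sided test comes close, at 70. At 36 per arm the two-sided test has about 71% power. The dropout step is right: 72 / 0.9 = 80. This discrepancy is a separate matter; the present point would stand even if 72 were exact.

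**2. Can the two proportions be attached to the primary outcome?**

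| | Sample size (2.13) | Primary outcome (2.10, Tables 1 and 2) |
|---|---|---|
| Construct | dependence | self-management |
| Scale | proportion | two questionnaires, no cut-off given |
| Respondent | survivors | survivors (SSSMQ) and caregivers (Family needs) |
| Number of tests | one | two instruments, no rule to combine them |

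Section 2.2 also lists self-management and independence in daily living as separate objectives. Nothing shown connects the left column to the right.

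**3. What the planned numbers give if the questionnaires are analysed as scores.** Section 2.14 would then use a t-test when normality holds. For an unadjusted comparison at two-sided 5% and 80% power, the detectable difference is about (1.960 + 0.842) × √(2/n) SD. The exact t-test value is slightly larger.

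| Per arm | Normal approximation | t-test |
|---|---|---|
| 36 (72 evaluable) | 0.66 SD | 0.67 SD |
| 40 (80 recruited, no dropout) | 0.63 SD | 0.63 SD |
| 20 (the 40 patients in section 2.4) | 0.89 SD | 0.91 SD |

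The documents give no SD or target difference for either questionnaire, so power can only be shown over an assumed range. At 36 per arm the t-test has these values:

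| Assumed difference | 0.3 SD | 0.5 SD | 0.6 SD | 0.8 SD |
|---|---|---|---|---|
| Power | 24% | 55% | 71% | 92% |

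**4. Two primary measures.**
- If either one at 5% counts as success, the overall error is 1 − 0.95² = 9.75% for independent tests. It is 9.1% at a correlation of 0.5 and 7.0% at 0.9.
- If both must be significant, the error stays at or below 5%. Two tests with 80% power each then give joint power of 0.80² = 64% if independent, and 75% at a correlation of 0.9.

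Under neither rule do a 5% level and 80% power both carry over unchanged from one test.

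**The case against.** **Section 2.13 does state a link, and the source of the 41.5% is not at hand.** This is fair. A reader might infer that the rate belongs to some other scale, but that cannot be shown from the document. What can be said is narrower: the article gives no definition by which either questionnaire yields that proportion. It may also be said that section 2.1 counts physical function within self-management. But section 2.10 then assigns physical function to the Barthel and Lawton indices, as secondary outcomes, so this does not supply the link.

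**The 5% level.** A reader might infer that the trial will exceed 5%, or that two instruments at two visits give four chances of success. The documents do not support this. Section 2.10 joins the instruments with a plain conjunction, which is compatible with requiring both, and then the level holds. The threshold in section 2.14 is a general convention, not a decision rule for the primary outcome. On timing, section 2.12 calls month 6 the final visit, and the Discussion bases the first analysis on the 6-month results. A success rule could also sit in the full protocol or an analysis plan that is not shown. Its absence from the article is therefore not an error in itself.

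**Plausibility of the drop to 15%.** It is tempting to doubt it because section 2.4 says most recovery has occurred by the chronic stage. That remark concerns brain repair and sets no limit on change in self-management.

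**The trial is called a pilot.** It is, in the abstract and in sections 2.4 and 2.10. But the title says Phase III, and section 2.13 makes an explicit 80% power claim. That claim has to be right or be withdrawn.

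The mismatch between sections 2.10 and 2.13 survives these points. An analysis plan could choose the deciding measure, but it could not turn a calculation on dependence into one on a self-management score.

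**Conclusion.** The power statement in section 2.13 is wrong as written, because it does not describe the analysis of the primary outcome in section 2.10. This rests on the text alone.

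The size of the gap depends on assumptions. If scores are compared by an unadjusted t-test, 36 per arm reaches 80% power only at 0.67 SD, and power lies between 24% and 92% for assumed differences of 0.3 to 0.8 SD. The true value in that range cannot be fixed from the document.

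On multiplicity the conclusion is conditional. The 5%/80% pair is not established for two primary measures: error up to 9.75% if either suffices, or joint power of 64% (independent tests at 80% each) if both are required. That the trial breaches 5% is not shown.

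The power statement should be corrected before the trial is analysed.

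**What to change.** - Name the SSSMQ score at the final visit, 6 months after baseline, as the single deciding primary endpoint, tested at two-sided 5%.
- Move the Family needs questionnaire and the month-3 scores of both instruments to secondary, reported with 95% confidence intervals.
- Replace the dependence-based paragraph in section 2.13 with the SSSMQ difference, in SD units, that the planned number can detect with 80% power: 0.67 SD at 36 evaluable per arm. State the planned number once, since section 2.4 speaks of 40 patients (0.91 SD at 20 per arm).

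No new instrument or visit is needed; both questionnaires are already scheduled. There are three costs. The caregiver questionnaire loses primary status, although caregivers are recruited too. The power statement becomes less favourable. And the change is a protocol amendment, which under section 2.15 needs Ethics Committee approval. Keeping both questionnaires as primary would also be legitimate if the success rule were stated, but the sample size would then have to be worked out for that rule.

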### 2.14. Statistical Analysis

Each variable will be characterized using frequency distributions central tendency, such as the mean and median, and to determine variability standard deviation or the interquartile range according to its distributional characteristics.

Comparisons between groups and intra-groups will be performed using parametric tests provided that the distributional characteristics of the data meet the requirements; otherwise, non-parametric tests will be used.

Comparisons between two continuous variables will be performed using the Pearson or Spearman correlation, depending on the distributional characteristics.

The comparison of proportions between categorical variables will be carried out by means of a chi-squared test or its corresponding Fisher correction. The continuous variables will be compared using the comparison of the means (t-student test or ANOVA) if the sample distribution is normal, and if the distribution is not normal, then the non-parametric Mann-Whitney U test will be utilized.

The populations will be analyzed by intention to treat analysis and as stated in the protocol.

A micro-data collection form will be developed. The analysis of costs will be done from the perspective of the health system and direct costs. The data collected will serve to estimate the actual cost of procedure data under usual practice conditions and costs derived from the implementation of the new intervention in the different contexts under study.

The collection of these data, together with data on effectiveness and utility, will enable subsequent studies on economic analysis and cost-effectiveness/utility to help decision-making on which alternatives are most effective and efficient from the point of view of the health system.

The SPSS 23.0 program for Windows (SPSS Inc, Chicago, IL, USA) will be used. A p-value of 5% or lower is considered to be statistically significant. The statistical analysis will be blind to the intervention group.

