## Abstract

Background: Stroke is a leading cause of severe and long-term disability in developed countries. Around 15 million people suffer a stroke each year, being most of them ischemic due to modifiable risk factors. Adequate self-management abilities may help to manage the consequences of stroke, but it is unknown which specific intervention could be effective to booster these self-management abilities. Objective: To evaluate the improvement of self-management in chronic stroke survivors using decision support and self-management system (STARR). Methods: A randomized, prospective, parallel group, open, and the unicentric pilot trial will be performed. Stroke survivors and their caregivers will be randomly allocated to STARR management or standard of care. Main inclusion criteria are mild to moderate disabled first stroke adult survivor, living at home, able to cope and follow the guidelines and devices, without socio-familial exclusion. All will get a conventional treatment in the acute and subacute phase; however, in the chronic period, cases will use the developed STARR App and Decision Support System. Measurements will be performed at baseline, at 3 months, and at 6 months. Outcome measures are patient-report outcome measure of self-management competency, physical function, risk factor reduction, healthcare resource utilization, knowledge of the condition, mood, and social isolation. Discussion: If effective, the results of this study will enable stroke patients and their caregivers to deal better with the everyday life obstacles of stroke, improve the adherence of the treatment, improve the control of cardiovascular risk, and, in consequence, reduce the recurrence of secondary strokes, the number of complications, the number of consultations, and readmissions; to ultimately reduce the health systems costs. Taking into consideration that the number of stroke survivors is increasing around the world, a large number of individuals could profit from this intervention.

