## Figures and Tables

**Figure 1 mps-02-00050-f001:**
[figure not shown]
Diagram of the study.

**Table 1 mps-02-00050-t001:** Schedule of the trial variables for patients.

Stroke Survivors	Variables/Scales	Event Visit (a) Month 0	Baseline Visit (b) Month 6	First Visit (c) Month 9	Final Visit (d) Month 12
Inclusion	Age	x	x		
	Stroke characteristics and type	x	x		
	Modified Barthel Index	x	x		x
	Modified Rankin Scale	x	x		x
	Mississippi Aphasia Screening Test [MAST]	x	x		x
	Montreal Cognitive Assessment [MoCA]	x	x		x
	Gijon’s social-familial evaluation scale	x	x		
	Comorbidities	x	x		
	Charlson Comorbidity Index	x	x		
Socio Demographic	Gender, ethnic group, deprivation index, hand dominance, education level, type of job, hobbies	x	x		
Clinical/ Neurological	Cardiovascular risk factors	x	x	x	x
	Neurological physical examination: Medical Research Council Scale [MRC]	x	x	x	x
	Mississippi Aphasia Screening Test [MAST]	x	x		x
	Montreal Cognitive Assessment [MoCA]	x	x		x
	Functional Ambulation Categories [FAC]	x	x	x	x
	10 m walking test/6 min walking test	x	x	x	x
	Berg Balance Scale [BBS]	x	x	x	x
	Frenchay Arm Test [FAT]	x	x	x	x
	Asworth Modified Scale for Spasticity	x	x	x	x
	Fatigue Severity Scale [FSS],	x	x	x	x
	Line Bisection Test	x	x	x	x
	Disphagia Sensitivity Campimetry	x	x	x	x
	Pain Analogic visual scale for pain Analgesic treatment consumption	x	x	x	x
	Depression and Anxiety: Golberg Scale	x	x	x	x
	Stress	x	x	x	x
	Weight, Height, BMI, waist size, waist-to-hip ratio	x	x	x	x
	Blood pressure, heart rate, glycemia	x	x	x	x
	Need of upper limb orthoses, lower limb orthoses, and canes and wheelchair use in outdoor activities	x	x	x	x
Health Literacy	Test of Functional Health Literacy in Adults Stroke Patient Education Retention	x	x		x
Usability	System Usability Scale			x	x
Life Style	Mediterranean Diet Assessment Tool Physical activity/Exercise Toxic consumption	x	x	x	x
Blood Test	Lipidic profile (total cholesterol, high-density lipoprotein (HDL), low-density lipoprotein (LDL), cholesterol), glycemia, proteins, albumin, HbA1c, Apoprotein B, and Apoprotein A1	x	x		x
Activities of Daily Living	Modified Barthel Index (BI) Lawton Index	x x	x x		x x
Quality of life	SF-36 Stroke Impact Scale (SIS)	x x	x x		x x
Self-Management	The Southampton Stroke Self-Management Questionnaire (SSSMQ)		x	x	x
	Satisfaction Questionnaire		x		x
	Quebec User Evaluation of Satisfaction with Assistive Technology			x	x
Adherence	Post-stroke checklist		x		x
	Non-pharmacological				

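### Continuous outcomes are compared without their baseline values, although these are collected; adjusting for them would gain precision in a small trial

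*Protocol article*

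**What the plan says.** Section 2.14 (Statistical Analysis) sets the test for continuous variables: "The continuous variables will be compared using the comparison of the means (t-student test or ANOVA) if the sample distribution is normal". Where normality fails, a rank test on two samples takes its place, again with no covariate. The same section also plans within-group tests: "Comparisons between groups and intra-groups will be performed using parametric tests provided that the distributional characteristics of the data meet the requirements". It mentions no covariate, ANCOVA, change score or repeated-measures model.

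The baseline values exist. The Abstract states: "Measurements will be performed at baseline, at 3 months, and at 6 months". Section 2.10 defines the primary outcome: "The proposed primary outcome will be measured by the validated Southampton Stroke Self-Management Questionnaire (SSSMQ) and Family needs of stroke patient questionnaire". Table 1 marks the SSSMQ at the baseline, first and final visits, and Table 2 does the same for the Family needs questionnaire. Table 1 also schedules baseline and final values for the SF-36, the Stroke Impact Scale, the Goldberg scale, the Berg Balance Scale, blood pressure, lipids and HbA1c.

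The trial is small on any reading: 40 patients in section 2.4; 72 evaluable and 80 recruited in section 2.13.

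**The concern.** A patient's score before the intervention usually predicts part of the score afterwards. A comparison that leaves it out treats this predictable part as noise, and the confidence interval is wider than the collected data require. With 20 to 40 patients per arm, that can decide whether a moderate effect is seen.

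Two other features of section 2.14 bear on the same choice. The switch to Mann-Whitney on observed normality lets the data decide whether the result is a difference in means or a rank comparison, and the rank test as stated takes no covariate. The within-group tests do use baseline, but only inside each arm, so they add nothing to the randomised contrast.

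**Working it through.** **The plan's own figure.** Section 2.13 derives 72 from 41.5% versus 15%, two-sided 5% and 80% power. The pooled formula, with mean proportion 0.2825, is

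n = [1.960·√(2·0.2825·0.7175) + 0.842·√(0.415·0.585 + 0.15·0.85)]² / 0.265² = 44.1, so 45 per arm, 90 in total.

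The 72 is not reproduced two-sided; a one-sided test gives 35 per arm, 70 in total. The dropout step is right (72/0.9 = 80). This is a separate matter. It concerns a proportion, and the 72 serves here only as a trial size.

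**Inputs.** Power 80% and two-sided 5% (section 2.13); 1:1 allocation (section 2.6); 36 per arm (72/2) or 20 per arm (40/2). The correlation ρ between baseline and final value is not in the document and is assumed at 0.3, 0.5 and 0.7. SDs are taken as equal at both times and in both arms.

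**Formulas**, with variances relative to a final-score comparison:
- final score: 1
- change score: 2(1 − ρ)
- ANCOVA: 1 − ρ²
- ANCOVA relative to change score: (1 − ρ²)/[2(1 − ρ)] = (1 + ρ)/2

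| ρ | ANCOVA / final score | Saving | Change / final score | ANCOVA / change | Saving |
|---|---|---|---|---|---|
| 0.3 | 0.91 | 9% | 1.40 | 0.65 | 35% |
| 0.5 | 0.75 | 25% | 1.00 | 0.75 | 25% |
| 0.7 | 0.51 | 49% | 0.60 | 0.85 | 15% |

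**Detectable difference.** The two-sample t-test gives 0.670 SD at 36 per arm and 0.909 SD at 20 per arm. (The normal approximation, (1.960 + 0.842)·√(2/n), gives 0.66 and 0.89.) Multiplying by √(1 − ρ²):

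| Per arm | Unadjusted | ρ = 0.3 | ρ = 0.5 | ρ = 0.7 |
|---|---|---|---|---|
| 36 | 0.67 | 0.64 | 0.58 | 0.48 |
| 20 | 0.91 | 0.87 | 0.79 | 0.65 |

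In patients: at ρ = 0.5, 72 adjusted patients carry the information of 72/0.75 = 96 unadjusted ones.

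**Cost of estimating the slope.** ANCOVA spends one degree of freedom. Allowing for it, with total N, the expected variance is (1 − ρ²)(N − 3)/(N − 4). Adjustment therefore gains when ρ² > 1/(N − 3): ρ above 0.16 at N = 40 (√(1/37)) and above 0.12 at N = 72 (√(1/69)).

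**The case against.** The strongest reply is that section 2.14 does not say whether the compared value is the final score or the change. Section 2.1 speaks of improvement, within-group comparisons are planned, and ANOVA could mean a repeated-measures model. A change-score reading would use baseline. This stands as a limit on the size: the savings against a final-score test hold only if final scores are compared. It does not rescue the plan, because ANCOVA has no larger variance than a change-score test at any correlation, apart from the one degree of freedom.

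Four stronger readings are tempting, and the document does not support them.
- A reader might infer that chance baseline imbalance biases the result. It does not: under randomisation the unadjusted test is valid and its standard error already allows for such imbalance.
- A reader might infer that the primary result is affected. Section 2.13 plans a chi-squared test of a proportion measured by the two questionnaires, so a comparison of mean SSSMQ scores as the primary analysis is not secured.
- A reader might fear that significance in one arm only will be taken as an effect. Nothing in section 2.14 says so; between-group comparisons are planned as well.
- A reader might take the gain at ρ of 0.5 to 0.7 as established. At 0.3 it is only 9%.

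**Conclusion.** The point holds as a matter of efficiency and should be acted on. The protocol itself names the tests, so this is a stated choice and not a detail left to an analysis plan that is not shown. The direction is secure for any correlation above about 0.16. The size is an assumption: a variance saving of 9% to 49% against final scores, or 35% to 15% against change scores, for correlations of 0.3 to 0.7. It applies to outcomes analysed as continuous and neither corrects nor changes the 72 in section 2.13.

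**What to change.** In section 2.14, analyse each continuous outcome that has a baseline value by ANCOVA: final-visit value on treatment and baseline value, with patients in the group to which they were randomised. Report the adjusted mean difference with its 95% confidence interval. Remove the normality switch and use a rank-based or bootstrap analysis as a sensitivity analysis. Report within-group changes descriptively, without p-values.

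No new data or visits are needed, and the named software can fit the model. It is more than a wording change in an analysis plan, however. The tests stand in the protocol, and section 2.15 requires the agreement of the principal investigator and the sponsor, and Ethics Committee approval, for a modification. It should be made before any unblinded analysis.
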